## Abstract

**Objective:**

Patients with cancer suffering from comorbid symptoms of depression need a psychotherapeutic treatment that is specifically tailored to the exceptional context of acute or chronic cancer treatment. The conceptualization of depression in Interpersonal Psychotherapy (IPT) is a promising framework for symptoms of depression in patients with cancer, because it focuses on coping with stressful life events, managing change and accessing social support.

**Method:**

The intervention was developed based on standard practice of group IPT for depression and adapted to the oncology setting by an expert panel. The IPT intervention comprises 10 weekly sessions of 60 minutes each. It is structured into modules incorporating IPT core themes: role transitions, grief, connection and interpersonal conflict. This feasibility study with an integrated qualitative study seeks to ascertain feasibility and acceptability of a larger trial of modified group IPT for adult patients with cancer within the context of a university clinics’ outpatient treatment. In addition, the study will enable first evidence of the intervention’s efficacy in reducing symptoms of depression and anxiety, and changes in interpersonal factors such as loneliness, thwarted sense of belonging, perceived burdensomeness, and perceived social support. Post-intervention semi-structured interviews will be recorded for qualitative content analysis.

**Conclusion:**

Our findings will suggest whether investigating group IPT as proposed is an acceptable, feasible and safe approach to ameliorate symptoms of depression in patients with cancer. The study is innovative in that it provides a new treatment to patients of different cancer types and treatment stages, creating a setting that is naturalistic and realistic in the context of psycho-oncology services.

## Introduction

The effects of cancer diagnosis and corresponding cancer treatment on the patients’ mental health have been well documented in the past decades (1–3). Across different populations and treatment settings one in two patients with cancer report significant distress (3), and a subset of 29% fulfill DSM-5 diagnostic criteria of mood disorders (2). Depression in patients with cancer can lead to poorer quality of life and that itself warrants psychological treatment. However, it also has effects beyond the mental health of the patients in that they are more likely to struggle with treatment decisions and may require more intensive attention from the medical team (4, 5). In addition, patients with cancer affected by depression are less likely to comply with treatment regimens (6), and untreated comorbid depression and distress have been linked to shorter survival in meta-analyses (7). Beyond that, the patients’ mental health affects their interaction with caregivers and thereby the caregivers’ well-being and caregiver burden. Therefore, comorbid symptoms of depression in patients with cancer warrant timely, specific, and intensive psychotherapeutic treatment (8). Standard psychotherapeutic treatment for depression, however, is not adapted to the specific context of symptoms of depression embedded in an oncological illness. There is a range of important characteristics that a specific psychotherapy for symptoms of depression associated with cancer should include:

Access to the psychotherapy should be low threshold, in order to facilitate enrollment for patients in crisis.It should keep the additional treatment burden on patients as low as possible and yield fast and palpable benefits to keep patients motivated and adhering.It should be feasible for patients and providers in diverse treatment stages and treatment settings of psycho-oncology care facilities.Conceptually, the psychotherapy should reflect the cancer-related etiology of symptoms of depression by addressing stressors specific to cancer patients’ experiences. Such stressors are, for example, changes in everyday life and relationships, declines in quality of life, struggles with treatment demands, communication with the medical treatment team, acute confrontation with mortality, isolation and lack of meaningful connection, and grief for a lost healthy self.The psycho-educative framework of symptoms of depression ought to be comprehensible and acceptable to patients with cancer and to their caregivers.The psychotherapy should be empirically tested for effectiveness and benefit for the patients.

There is one framework for the psychotherapeutic treatment of depression that appears to be an ideal fit with the needs and requirements of this patient group: it is the conceptualization of depression in Interpersonal Psychotherapy (IPT).

IPT was developed by Klerman et al. (9) to provide treatment for episodic unipolar depression. Drawing on the interpersonal theory of psychiatry by Sullivan (10), and on J. Bowlby’s attachment theory (11) as expanded on by Rutter (12), they conceptualized the development of symptoms of depression as inextricably intertwined with interpersonal factors such as social roles, interpersonal relations, and life events. IPT sees interpersonal difficulties as both antecedents and consequences of clinical depression, with the two continuously reinforcing each other. The interpersonal approach to treating depression is to ameliorate the patients’ interpersonal difficulties, centered in four focal areas: role transitions, conflict, isolation and loneliness), and grief besides building up social support. The patient is educated about depression and assigned the ‘sick role’ (13). This clarifies that the patient is temporarily in need of help and takes away the burden of responsibility, guilt or shame for the symptoms.

The effectivity of IPT in treating depression has been thoroughly evaluated (14) and IPT is among the recommended treatments for depression in international practice guidelines (15). IPT has also proved effective in treating anxiety disorders (16). Globally, IPT has been applied to highly diverse patient populations in a variety therapeutic settings (17).

The interpersonal conceptualization of symptoms of depression is plausible and acceptable to patients with cancer and their relatives or caregivers, because it offers them not yet another incomprehensible diagnosis but a rationale with a comprehensible, strategic treatment plan. By taking on the ‘sick-role’, patients learn to understand their depressive symptoms not as a personal failure, but as a reaction to the marked changes in important interpersonal areas brought on by the cancer diagnosis and treatment.

The focal areas of IPT (role transition, interpersonal disputes, isolation, grief) can also be applied to the context of oncology with significant benefit, as is shown in (**Figure 1**). As in the Interpersonal and Social Rhythm Therapy, an adaptation of IPT for bipolar disorder (18), the focal area of “grief” targets expression of grief over the “lost healthy self”.

**Figure 1 f1:**
[figure not shown]
Application of Interpersonal Psychotherapy Focal Areas in Cancer.

IPT has been applied successfully to depression in other populations, such as HIV-seropositive patients (19), patients with heart disease (20), patients in rehabilitation after a stroke (21) and elderly patients (22). We assume that these patient groups share important characteristics with patients with cancer. They, too, may be faced with role transitions concerning loss of activity, strength, autonomy, and perceived immortality. Moreover, they may also be forced to navigate novel interpersonal challenges, and may face similar conflicts caused by the role transitions brought on by their health conditions. They may experience loneliness and isolation, feeling stigmatized and disconnected from their peer group. They, too, may be reminded of past losses of loved ones to similar ailments. The applicability of IPT in these conditions speaks to the conceptual applicability of IPT for patients with cancer.

A current systematic review of randomized controlled trials of IPT applications in oncology (23) shows a paucity of research on the subject. Six studies focused on remote Interpersonal Counselling (IPC), a shorter, more accessible form of IPT developed for primary health care settings (24–30). Results regarding the efficacy of remote IPC in oncology settings were inconclusive (23). Two studies investigated individual IPT in oncology settings. IPT proved to be superior to treatment as usual in reducing symptoms of depression in patients with cancer both these trials (31, 32).

A group psychotherapy concept appears to yield added benefits in the context of psycho-oncology, considering the alienating and isolating experiences of patients with cancer. Sharing with a group of similar experience can offer patients relief by normalizing psychological distress and stressors. From the very first session on, the group can offer patients a sense of connection, acting as a first intervention towards decreasing loneliness. Group members can also provide useful feedback when tackling interpersonal skills and conflicts. Thus, the group will aid in decreasing the psychological burden and in increasing motivation to keep participating.

The effectiveness of group IPT has been assessed in different populations, and for a variety of disorders, such as depression, binge eating disorder, and posttraumatic stress disorder (33), but so far not for depression in patients with cancer (23). Therefore, the aim of this study is to develop an IPT group program tailored specifically to the needs of patients with cancer and conduct a preliminary evaluation of the program. An effective, accessible treatment for symptoms of depression in patients with cancer will improve health care for patients with cancer not only by improving their quality of life and alleviating mood disturbance, but also by enabling them to more thoroughly adhere to cancer treatments.

## Objectives and research questions

The object of this study is to assess the feasibility and acceptability of modified group IPT for patients with cancer in outpatient settings in a longitudinal study design, and identify barriers and facilitators to the implementation of the intervention. The study also aims to preliminarily ascertain effects of the treatment to alleviate depression in patients with cancer and to reduce further facets of psychological burden (anxiety, cancer-related psychological distress, loneliness, perceived burdensomeness, thwarted belongingness) and improve perceived social support. All data collected will be used to inform the decision on progression to a full trial.

## Methods and analysis

### Study design

The study is a feasibility study, more specifically an internal non-randomized pilot study according to the framework proposed by Eldridge et al. (34), with an integrated qualitative study. It is designed to investigate the feasibility and preliminary efficacy of adapted group IPT for cancer patients in outpatient settings and therefore corresponds to steps one (feasibility) and two (efficacy) of the Translational Research Framework (35), guiding implementation research in health services. The obtained data will be used to inform a broader trial of the intervention.

The trial flow is shown in (**Figure 2**). Informed consent will be obtained before participation. Participants will then complete the assessments online using the REDCap survey tool (36, 37). For an overview of diagnostic instruments, see (**Table 1**). After participating in the 10-week modified group IPT intervention, they will complete the same assessment again at T1. The post-intervention interview will be audio-recorded for analysis. Assessments will be repeated at follow-up T2 three months after completion of the intervention. The intervention is considered completed when participants have attended 8 out of the 10 sessions.

**Figure 2 f2:**

Trial Flow.

**Table 1 T1:** Assessment schedule.

Measures			Baseline (T0)	Post-treatment 10 weeks after baseline (T1)	3- months follow-up (T2)	6-months follow-up (T2)
Sociodemographic and medical data			x	x (shortened^1^)	x (shortened^1^)	x (shortened^1^)
Primary Outcome	Symptoms of Depression	PHQ-9	x	x	x	x
Secondary Outcomes	Symptoms of Anxiety	GAD-7	x	x	x	x
	Psychological Distress	DT analogue scale and problem areas	x	x	x	x
Tertiary Outcomes (Mechanisms)	Loneliness	R-UCLA	x	x	x	x
	Perceived Social Support	BS6	x	x	x	x
	Interpersonal Needs	INQ	x	x	x	x
interpersonal stressors		Self-generated items	x	x	x	x
Quality of Life		EQ-5D-3L	x	x	x	x
Need for psychosocial support		HSI	x	x	x	x
Acceptability and Feasibility		Self-generated items		x		

DT, Distress Thermometer; HSI, Hornheider Screening Instrument; GAD-7, Generalized Anxiety Disorder Questionnaire; PHQ-9, Patient Health Questionnaire; R-UCLA, Revised UCLA Loneliness Scale; BS6, Brief Social Support Scale; INQ, Interpersonal Needs Questionnaire

^1^ items omitted at follow-up: age, gender, past psychiatric disorder, cancer entity, date of first cancer diagnosis

Results will be published according to CONSORT reporting guidelines (CONSORT 2010 statement: extension to randomised pilot and feasibility trials, 38), excluding the randomization section.

### Participant eligibility

Participants will be included provided they are 18 or older, give written, informed consent, have a diagnosis of cancer and are willing and able to participate in the online assessments and 10 weekly sessions of group IPT in person. A further inclusion criterion is self-reported symptoms of depression (rating of 3 or higher in PHQ-2). Since there are no exclusion criteria regarding time since cancer diagnosis, self-reported cancer-related distress (DT≥ 4) is used as an inclusion criterion as well, to ensure participants consider their cancer diagnosis relevant to the symptoms they are experiencing. Participants will be excluded if they report comorbid psychiatric disorders requiring more intensive treatment (acute psychotic symptoms, acute manic episode, acute suicidality, acute substance use disorder excluding nicotine) within the past four weeks, and if they are currently in regular treatment with a psychotherapist. Patients receiving antidepressant medication will be included if they agree to stay on a stable dose and medication throughout their participation in the study and agree to report changes in medication. There are no exclusion criteria regarding type of cancer or cancer treatment stage.

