### Participant recruitment

Participants will be recruited from the pool of patients receiving treatment in oncological facilities of the University Hospital Tübingen (UKT), and the Comprehensive Cancer Center Tübingen-Stuttgart including the psychosocial counselling facilities (Krebsberatungsstelle Tübingen) using flyers, posters, social media outlets and information provided by nurses, doctors, and psychologists. Patients in in- and outpatient oncological care at the UKT complete an electronic psycho-oncological screening (ePOS) as part of routine cancer patient care and are approached by the psycho-oncology services if indicated (see 39, 40). If they indicate symptoms of depression (rating of 3 or higher on PHQ-9), psychological distress (rating of 4 or higher on DT analogue scale) on the ePOS, their psycho-oncologist will ask if they are interested in participating in the study. Participants who indicate interpersonal distress (i.e. “no” for “Do you have someone to talk to about your worries”, “yes” for “familial problems”) will also be informed about the program and will be included in the pilot study if they meet the inclusion criteria. Information about the treatment program and ways of referral will also be sent out to practitioners who might treat cancer patients (general practitioners, oncologists, gynecologists, urologists, neurologists, surgeries, etc.) in the area around the clinic. Questions regarding the study will be answered via email, phone or in person. Those seeking participation will be screened for inclusion and exclusion criteria. Participants will not receive compensation for participating in the study. Recruitment will end when 40 patients have completed assessments. For the qualitative study, recruitment will end when saturation is reached as described below.

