Primary outcome will be symptoms of depression at completion of the treatment and 3-months follow-up, which will be assessed using the Patient Health Questionnaire (PHQ-9). As secondary outcomes we chose symptoms of anxiety, which will be assessed using the Generalized Anxiety Disorder Questionnaire (GAD-7), and psychological distress as measured by the Distress Thermometer (DT) at completion of the treatment and 3-months follow-up. Tertiary measures are self-reports of loneliness as measured by the R-ULCA Loneliness Scale, perceived social support as measured by the Brief Social Support Scale (BS6), interpersonal needs (perceived burdensomeness and thwarted belongingness) as measured by the Interpersonal Needs Questionnaire (INQ) at completion of the treatment and 3-months follow-up.

Qualitative data will consist of the audio recording of the post-intervention semi-structured interviews. Records will be saved using the patient pseudonym on study tablets that are not connected to the internet and will be transcribed by the study team. Recordings will be deleted after analysis is completed. A translation of the interview guidelines can be seen in (**Table 4**).

**Table 4 T4:** Post-intervention semi-structured interview.

Topic	Question
Goal achievement and relevance to everyday life	In the preparatory session, you formulated the following goal for the group therapy: X What has changed in relation to X since the start of therapy? How do you notice the change in everyday life? What would you say - have you achieved, partially achieved or not achieved the goal? Which aspects of the group therapy did you find helpful regarding X? Which aspects did you find inappropriate or not useful? Have there been any changes in your everyday life beyond the goals we just talked about? How do you observe these changes? How is the change related to the group therapy? What interpersonal experiences do you take away from the group?
Challenges and adverse effects	What were the particular challenges or difficulties for you in group therapy? How did the therapists or the group support you in overcoming the challenges? (How could the therapists or the group have supported you better in overcoming the challenges?) Did group participation have adverse effects for you?

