### Sample size calculation and statistical analyses

All quantitative data analyses will be conducted using R (61), RStudio (62), and MATLAB (60).

Due to the nested nature of group intervention data (63) and more specifically the scarcity of research regarding IPT in patients with cancer other than breast cancer, sample size calculations are to be treated with caution. A sample size of 40 participants is considered appropriate for this feasibility study.

Feasibility outcomes will be analyzed using percentages. Descriptive analyses of sociodemographic data will be conducted. Preliminary efficacy will be analyzed in within-subject comparisons for each outcome measure and reported with 95% confidence intervals (CI). Results regarding the primary outcome (symptoms of depression, PHQ-9) will be considered indicative of efficacy if the CI is above zero and includes the predefined Minimal Clinically Important Difference (MCID) of 5 points as previously determined by Löwe et al. (64). Results regarding secondary and tertiary outcomes will be considered indicative of efficacy if it is above zero.

Missing data will be reported as such. It is expected that at least a subset of dropouts may nevertheless be available to complete the post-treatment assessment, improving the accuracy of data collected. An interim analysis is not planned.

Qualitative analysis will be conducted using MAXQDA 2022 software (65). Record transcripts will undergo qualitative content analysis as described by Mayring (66) using deductive-inductive category formation, starting with an initial batch of 6 interviews. Iterative analysis will continue until saturation is reached. Procedures and results will be recorded and reported in accordance with the Standards for Reporting Qualitative Research (SRQR) (67). Saturation will be assessed using the 16-item checklist provided by Ahmed (68). Saturation will be defined as lack of emergence of new themes in three consecutive interview transcripts. Meta-analysis indicates a sample size of 13 is enough to reach saturation for most studies (69). Analysis will focus on the following aspects included in the semi-structured interview (**Table 4**): changes in everyday life, helpful elements of group IPT, inappropriate elements of group IPT, interpersonal experiences in group IPT, challenges in group IPT, support regarding challenges, adverse effects, barriers and facilitators for participation in group IPT and study procedures, and outlook.

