## Discussion

In this pilot study in 40 patients, we propose to develop and evaluate an IPT group treatment for symptoms of depression specifically tailored to the needs of patients with cancer and comorbid symptoms of depression.

The described study is a pilot study, and information gathered will be limited by the exclusive use of self-report data and the naturalistic design without any control group. A lack of resources, potential difficulties in recruiting participants and ethical considerations led to the decision not to apply a randomized controlled design.

The naturalistic group composition of patients with diverse types of cancer and in different treatment stages increases the generalizability of findings from this study. It also adds to its value for care providers within the psycho-oncological services who also treat patients from all specialties and at all points in the patient journey. Participants may even profit from the different perspectives and experiences shared in more heterogenous groups.

Our preliminary findings will suggest whether a trial of group IPT is feasible and indicate preliminary efficacy in reducing symptoms of depression in patients with cancer. We will also assess changes in symptoms of depression, anxiety, and in interpersonal factors such as loneliness, thwarted sense of belonging, perceived burdensomeness, and perceived social support. The findings will inform us how to adapt and change the program in order to make it more efficient or feasible for patients and care providers. Qualitative content analysis will enrich our understanding of the lived experience of participants regarding feasibility and acceptability of intervention and study procedures and provide qualitative insight into everyday changes for patients.

Adequate and efficient treatment for depressive symptoms in patients with cancer is urgently needed. The proposed group IPT program adapted for cancer is a novel, unique and promising approach to the problem. An effective treatment for symptoms of depression in patients with cancer is highly relevant because depressive symptoms affect a large proportion of patients with cancer, and have detrimental effects on patients’ quality of life, treatment compliance, and even mortality (5).

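### Entry requires high DT and PHQ-2 scores, so zero is not a valid no-effect reference for uncontrolled change in DT or, depending on the retest correlation, in PHQ-9

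*Protocol article*

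**What the plan says.** Protocol article, Participant eligibility, sets two floors on self-reported scores: "A further inclusion criterion is self-reported symptoms of depression (rating of 3 or higher in PHQ-2", and "self-reported cancer-related distress (DT≥ 4) is used as an inclusion criterion as well". Participant recruitment adds that patients are approached because of raised routine screening scores: "If they indicate symptoms of depression (rating of 3 or higher on PHQ-9), psychological distress (rating of 4 or higher on DT analogue scale".

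Preliminary efficacy outcomes then uses the same constructs as endpoints. For PHQ-9: "Primary outcome will be symptoms of depression at completion of the treatment and 3-months follow-up". For the secondary outcome: "psychological distress as measured by the Distress Thermometer (DT) at completion of the treatment and 3-months follow-up".

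Sample size calculation and statistical analyses compares each measure within subjects with a 95% confidence interval. The PHQ-9 interval must lie above zero and also include the 5-point MCID. For the other outcomes zero alone decides: "Results regarding secondary and tertiary outcomes will be considered indicative of efficacy if it is above zero". I read the pronoun as the confidence interval and improvement as positive change.

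The abstract says that "the study will enable first evidence of the intervention’s efficacy". The Discussion lists the "naturalistic design without any control group" among the limitations. It does not mention regression to the mean.

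**The concern.** A patient admitted because a score is high has, on average, a score partly raised by measurement error or a passing bad spell. On re-measurement the group mean moves back towards that of the source population without any treatment. Some patients also recover spontaneously over ten weeks. Without a control group, neither can be separated from the effect of the therapy.

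The decision rule takes zero change as the mark of no effect, and after this selection that need not be so. DT is the clean case: the same scale is used for entry and for outcome, and zero is the only bar. For PHQ-9 the overlap is partial (two items of nine) and the bar is higher, but selection on a correlated score is enough for regression to occur.

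At stake is the meaning of the prespecified verdict. Followed exactly, the rule could report efficacy for a treatment that does nothing.

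**Working it through.** **Inputs from the article.** Entry at PHQ-2 ≥ 3 and DT ≥ 4; N = 40; 95% interval on within-subject change; PHQ-9 rule (interval above 0 and including 5); DT rule (interval above 0); T1 ten weeks after baseline. The article gives no SD of change, retest correlation or formula behind N = 40, so there is no stated figure to reproduce.

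**Step 1: mean change each rule needs.** Half-width = t(0.975; 39) × SD / √40, with t = 2.02. The SDs of change are assumptions.

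- PHQ-9, SD 5: half-width 1.60, so the mean must lie between 5 − 1.60 = 3.40 and 5 + 1.60 = 6.60. For SD 4 the range is 3.72 to 6.28; for SD 7 it is 2.76 to 7.24.
- DT: the mean must exceed 0.64 for SD 2, 0.80 for SD 2.5 and 0.96 for SD 3.

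**Step 2: simulation with zero treatment effect.** Nine PHQ items scored 0 to 3 and a 0 to 10 DT share a common factor. The assumed unselected PHQ-9 has mean about 6 and SD 5.6; the assumed DT has mean 5 and SD 2.7. Patients are selected on both floors, with 40 per trial. Latent ten-week correlation runs from 0.5 to 0.8. Clustering by therapy group, dropout and natural recovery are left out. There are three cases for T0:

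- A: T0 is the screening score.
- B: T0 is taken two weeks after screening, and scores drift back gradually (AR(1)).
- C: T0 is a separate measurement, with a stable trait plus independent noise at each occasion.

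| Latent correlation | 0.5 | 0.6 | 0.7 | 0.8 |
|---|---|---|---|---|
| A: mean DT fall | 1.1 | 0.9 | 0.7 | 0.5 |
| A: DT rule met | 82% | 72% | 57% | 42% |
| B: DT rule met | 69% | 60% | 49% | 39% |
| A: mean PHQ-9 fall | 4.5 | 3.7 | 2.8 | 2.0 |
| A: full PHQ-9 rule met | 93% | 75% | 35% | 3% |
| B: full PHQ-9 rule met | 78% | 57% | 22% | 1% |

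In case C the mean fall is about 0, the DT rule is met in about 2.5% (one tail of a 95% interval), and the full PHQ-9 rule in under 1%.

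**Step 3: checks by hand, case A.**

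- Size of the PHQ-9 fall: (1 − r) × (selected mean − unselected mean). At latent 0.8 the simulated PHQ-9 correlation is 0.76 and the means are 14.2 and 6.1, so 0.24 × 8.1 = 1.9, against 2.0 simulated.
- DT at 0.5: fall 1.12, SD of change 2.4, SE = 2.4/√40 = 0.38, half-width 0.77. P = Φ((1.12 − 0.77)/0.38) = Φ(0.92) = 0.82.
- PHQ-9 at 0.8: fall 1.99, SD 4.8, SE 0.76, half-width 1.54, so the mean must reach 3.46. P = 1 − Φ((3.46 − 1.99)/0.76) = 1 − Φ(1.93) = 0.03.

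The 5-point condition therefore protects PHQ-9 well at correlation 0.8 and partly at 0.7. At 0.5 to 0.6 it gives little protection, because an interval that merely reaches up to 5 passes.

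**The case against.** **The limitation is disclosed and the claims are hedged.** The article calls its evidence first and preliminary, admits the missing control, and makes adherence the primary progression criterion. That stands: an uncontrolled pilot is legitimate, and this verdict is not the main basis for going on or stopping. But a limitation in the Discussion leaves the rule in the analysis section as it is.

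**T0 is probably not the screening score.** Study design puts the online assessment after consent, Table 3 places consent in the individual pre-group session, and Participant recruitment describes screening as its own step. A reader might infer from the absence of a screening column in Table 1 that eligibility answers serve as T0. The documents do not support that: Table 1 schedules outcome assessments, and the trial-flow figure is not available. Nor do they say that T0 is a fresh measurement without a cut-off. Case B also shows that a later T0 helps fully only if the excess at screening has already gone.

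**The primary rule is not a test against zero.** This stands. A reader might infer that regression alone would routinely satisfy the primary outcome rule. The additional MCID condition rules that out as a general statement.

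**The inputs are assumed.** This stands too. Recruitment by flyers, social media and referral may draw an already distressed pool, which would reduce the gap and the fall.

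**Consequence for the larger trial.** A reader might infer that the pre-post change will become its effect-size assumption. The article says only that the data will inform progression and a broader trial.

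**Conclusion.** The point holds in a limited form. With entry floors on DT and PHQ-2 and no control group, zero change is not a sound no-effect reference, and the rule can return an efficacy verdict without a treatment effect.

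- **DT:** about 40 to 80% of null trials if T0 is the screening score or shortly follows it with gradual regression; about 2.5% if T0 is separate with independent occasion noise.
- **PHQ-9, full rule, in the first two cases:** about 1 to 3% at correlation 0.8, rising to 57 to 93% at 0.5 to 0.6; under 1% in the third case.

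These figures rest on assumed score distributions and correlations, and they ignore clustering and dropout. They show what the rule permits; they do not predict this trial's result. Natural recovery is not included and would add to the change in every case, including the third.

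**What to change.** 1. In Participant eligibility and Study design, state that eligibility rests on the ePOS or screening answers, and that T0 PHQ-9 and DT are a fresh administration to which no cut-off is applied. In the same edit, reconcile the two sections that attach the cut-off of 3 to different scales (PHQ-2 under eligibility, PHQ-9 under recruitment).
2. Where screening scores are kept, report the shift from screening to T0 in PHQ-2 and DT. It gives a direct view of regression before treatment starts.
3. In Sample size calculation and statistical analyses, call results that meet the rules indicative of pre-post improvement instead of efficacy, and adjust the abstract to match. This is needed even with a fresh T0, because gradual regression and natural recovery remain.
4. Name regression to the mean in the Discussion next to the missing control group.

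The cost is wording and the retention of screening scores where they exist. No clinical procedure, sample size or progression criterion changes, and the article reports only 6 participants recruited by 10/24. The downside is a more modest claim.
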